### Frequency and plans for auditing trial conduct {23}

The research team will meet regularly once a week to discuss participant and intervention progress, emerging challenges, and required adjustments to the protocol. These meetings will also serve to monitor data on outcomes and adverse events, and to oversee participants’ safety. A data monitoring committee will not be needed for the SUFHA trial, given that the interventions are non-invasive with minimal risk of harm.

### Plans for communicating important protocol amendments to relevant parties (e.g., trial participants, ethical committees) {25}

If any changes to the protocol are needed, our plan is to first notify the sponsor and funder. Then, the principal investigator (PI) will notify the ethical commission and send a copy of the revised protocol to be added to the research center CIDEFES project management database. Any deviations from the protocol will be fully documented under a report sent to the CIDEFES. This way, we can maintain transparency and accountability throughout the study.

Finally, we will update the protocol in the clinical trial registry to ensure that all stakeholders have access to accurate and up-to-date information about the study.

### Dissemination plans {31a}

The rationale for this project entails novelty and generates new knowledge enough to publish at least 3 scientific papers in international peer-review Journals. (1) protocol publication; (2) main results from the intervention considering the several outcomes; (3) main results from the follow-up phase.

Furthermore, these findings will be initially presented at international and national conferences. Additionally, to disseminate the project on a larger scale, there is a plan to develop four short cut videos depicting the several phases of the project. These videos will be created by the HEI-Lab researchers, along with bachelor and master students from their faculty, and shared with the Lusófona University. The goal is to highlight the chronology of the project, and to stimulate the uptake of this type of intervention by disseminating participants’ experiences as they were shaped by the project: The first clip will show the participants in the baseline assessments. The second video will highlight the initial session. The third clip, released on the fourth month of the project, will focus on the intervention and the new reality of the participants. The fourth clip, released towards the end of the sixth month of intervention, will focus on the main changes the participants feel from a longer use of the sit-stand desks and other aspects not mentioned in the prior video. Finally, a fifth clip will be released in the follow-up period and will feature the study’s main findings and testimonies from the participants, including adaptations made.

## Discussion

Albeit the strong evidence on the health benefits of active lifestyles, an alarming proportion of adults continues with sedentary lifestyles, with an increasing trend in the prevalence of SB [72]. SB is something particularly worrying, considering that worldwide, adults spend more than 60% of their waking time in a sitting position, with most of that time taking place during work [73, 74]. To counteract this trend in office workers, it is important to apply strategies so that workers can reduce the time spent sitting and increase the time in a standing posture, using short and active breaks during their working hours [75]. One potential solution is the introduction of sit-stand desks in the workplace. Although scientific evidence is limited on this topic, sit-stand desks seem to reduce SB among office workers [76, 77] and consequently they may improve worker’s health, without compromising productivity and concentration [76, 78].

This paper describes the protocol of the SUFHA, a study designed to assess the effectiveness of a 6-month sit-stand desk workplace intervention offered to university staff, to reduce prolonged sitting and increase standing and interruptions in sitting time.

Besides the introduction of a contextual change in the workplace (i.e., sit-stand desk), this intervention will use an initial psychoeducational session to all participants, to inform about the harms of spending too much time sitting and the independent health benefits of interrupting this behavior more often. Furthermore, a motivational system of prompts will also be offered, nudging participants to stand more often, for 6 months. After the initial 6 months of the intervention, the control group will receive the sit-stand desk, and the intervention group will be without the stimulus, to observe if the new habits gained during the intervention period somehow remain after 3 months of follow-up (i.e., without the sit-stand desks). A major strength of the SUFHA is that it builds on previous interventions using sit-stand desks around the globe to target office workers in a university setting. Previous interventions have been combining sit-stand desk in addition to other strategies (i.e., multicomponent interventions) such as the usage of pedometer and/or competition among participants, or other strategies [79, 80], which makes it difficult to isolate the impact of simply using these sit-stand desks; SUFHA intends to fill this gap and extending it by providing data on maintenance of the new habits. Furthermore, feedback on the barriers and facilitators of the use of the sit-stand desks will also be collected via focus groups exploring the experiences of the participants during the trial.

The findings from this cluster RCT will provide insight for future research studies, as well as real-world interventions, and offer evidence for policy guidelines around workplace health and well-being.

The current RCT intends to inform employers and nudge them to invest in their occupational health conditions by providing evidence on the impact of using sit-stand desks. Furthermore, a refined, low-contact intervention informed by participants’ experiences will be available to be disseminated and implemented in diverse occupational settings, including the health sector, raising awareness for the positive impact of the use of sit-stand desks in multiple work settings. We hope that project findings and materials can help to nudge public and private companies from all sectors (e.g., education, health, industry, services) to adapt their work settings to use sit-stand desks, thus translating research into the “real world.” We anticipate important health benefits from this intervention, including improvements in eating patterns, as well as gains in work engagement that may convince companies and governments to invest in these new approaches, which will nurture the sustainable implementation of preventive interventions tailored to the work context, improving employee’s agency, movement behaviors, and well-being to ultimately halt the rise of NCDs and associated healthcare costs.

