**Methods:**

A two-arm (1:1), superiority parallel-group cluster RCT will be conducted to evaluate the effectiveness of this intervention in a sample of office-based workers from a university in Portugal. The intervention will consist of a psychoeducation session, motivational prompts, and contextual modification promoted by a sit-stand desk in the workplace for 6 months. The control group will work as usual in their workplace, with no contextual change or prompts during the 6-month intervention. Three assessment points will be conducted in both groups, pre-intervention (baseline), post-intervention, and a 3-month follow-up. The primary outcomes include sedentary and physical activity-related variables, which will be objectively assessed with 24 h monitoring using the ActivPAL for 7 days. The secondary outcomes include (a) biometric indices as body composition, body mass index, waist circumference, and postural inequalities; and (b) psychosocial variables such as overall and work-related fatigue, overall discomfort, life/work satisfaction, quality of life, and eating behavior. Both the primary and secondary outcomes will be assessed at each assessment point.

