## Interventions

### Explanation for the choice of comparators {6b}

SUFHA is designed for a sample of adult University office workers and will consist of two groups. A waiting-list control group will only attend a psychoeducational session regarding the independent benefits of reducing and interrupting sitting time with standing, with no contextual change during the 6-month intervention (i.e., no access to the sit/stand desk). The intervention group will attend the psychoeducational session and will be provided with the opportunity to have a sit-stand desk in their workplace, allowing them to work seated or standing and change between these postures as many times as they desire for 6 months.

After the intervention period, the waiting-list control group will have access to the sit-stand desk.

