There is evidence that temporary context changes, such as holidays, threaten to derail newfound routines, such as standing more often in the workplace [39]. Furthermore, after the intervention period, participants will no longer have the sit-stand desk. Thus, to enhance motivation and self-regulation for internalizing the new routines of breaking up sitting time, intervention participants will also be provided motivational nudges throughout the intervention. Delivery of these nudges will vary from 4 times in the first month, to 2 times in the second and third months, and monthly until the end of the intervention. These motivational nudges will be delivered in different formats, designed to be appealing and engaging (e.g., animated short videos containing simple tips on different forms of breaking sitting time and benefits of that); social support and social modeling will also be enhanced via these nudges (e.g., including testimonials from study participants willing to share their ongoing experience, including photos and short videos using the desk) allowing to support relatedness, perceived competence, and autonomy to use the desk. These are the three basic psychological needs supporting autonomous motivation according to Self-Determination Theory [60]. This type of motivation, in turn, has been shown to allow the integration of new health behaviors in the long term while also enhancing well-being [61].

To determine if the outcomes’ changes observed during the 6 months of work can be maintained in a context without the stimulus (i.e., no sit-stand desk), the intervention group will be followed for 3 months, in which they will be without the sit-stand desks. By the end of the intervention period and at the end of the follow-up, assessments will be conducted, and feedback provided to all participants assuring valuable information regarding participants sedentary patterns, body composition, eating patterns, health and work-related outcomes, fatigue, presenteeism, job satisfaction, well-being, and quality of life, and information on how these have changed over the course of the study.

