### Provisions for post-trial care {30}

We do not expect any harm from this intervention, as we are providing the opportunity for both groups to experience working on a sit-stand desk, without a mandatory amount of change. Regulation of the amount of sitting time replaced by standing will be settled by each participant, informed by information provided in terms of safety and progression given in the initial psychoeducational session and at the time of desk installation. To enhance the internalization of the new habits of breaking sitting time potentially raised by the sit-stand desk, motivational prompts to enhance autonomous motivation and self-regulation in the long term (after intervention-end) will also be provided.

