### Plans to promote participant retention and complete follow-up {18b}

Assessments will be conducted by the end of the intervention period and at the end of the follow-up. To maximize retention at all assessments we will:Send participants an advance reminder that measurements are upcoming, using a personalized email sent 2 to 3 weeks ahead of the measurement dates, complemented by a phone call to confirm/arrange an appropriate appointment time (suited to participants schedules).Send a confirmation of the date, time, and location (always inside the campus of the university, in a calm and adequate location).Text participant in the previous day leading up to their appointment to remind them about the time, date, and location.

To enhance overall adherence to assessment periods, feedback will be provided at the end, to all participants, assuring valuable personal information regarding participants sedentary patterns, body composition, eating patterns, health and work-related outcomes, fatigue, presenteeism, job satisfaction, well-being, and quality of life, and information on how these have changed over the course of the study. The control group will only receive that feedback on the second evaluation moment, as providing feedback on the baseline can influence their actions during the control phase, which is not desired.

The value, detail, and richness of the information provided via these assessments will be highlighted since the beginning of the study, for example in the dissemination contacts/explanation of the trial, as well as in the initial psychoeducational session. Furthermore, this initial session will highlight the importance of participation in the trial (description of how important RCTs are for science will be embedded in the information provided), and thus, reducing the risk of dropout. The control group (in higher risk of dropping out in the absence of intervention) will also be provided with the opportunity of having the intervention (waiting-list group) after the 6-month assessment period.

During the trial, a website will be nurtured with interesting information (i.e., short films highlighting the evidence-based benefits of sit-stand desk usage; shortcuts highlighting the several phases of the study with the inclusion of the participants (see Intervention description {11a} for more details).

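### The Discussion says the trial isolates the sit-stand desk, but only the desk arm gets motivational nudges, so the 6-month contrast estimates a package and not the desk alone

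*Protocol article*

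**What the plan says.** The Discussion faults previous trials for pairing the desk with other strategies, "which makes it difficult to isolate the impact of simply using these sit-stand desks; SUFHA intends to fill this gap", and then speaks of "extending it by providing data on maintenance of the new habits". Objectives {7} likewise describes the change as resulting from the contextual modification, with the desk as its only example.

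The intervention is defined more broadly elsewhere. The abstract's Methods state: "The intervention will consist of a psychoeducation session, motivational prompts, and contextual modification promoted by a sit-stand desk in the workplace for 6 months". Intervention description {11a} says that "intervention participants will also be provided motivational nudges throughout the intervention". It also adds a desk demonstration, ergonomic information, individual guidance on building up standing time, and a flyer.

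For controls, the abstract says: "The control group will work as usual in their workplace, with no contextual change or prompts". Explanation for the choice of comparators {6b} says: "A waiting-list control group will only attend a psychoeducational session". The psychoeducational session is given to both arms according to {6b}, {11a}, Strategies to improve adherence {11c} and the Discussion.

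Two further statements bear on the comparison. Provisions for post-trial care {30} mentions prompts to support motivation and "self-regulation in the long term (after intervention-end) will also be provided". Plans to promote participant retention {18b} says: "The control group will only receive that feedback on the second evaluation moment".

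**The concern.** The protocol claims a property that its design lacks. It presents the trial as the answer to a weakness of multicomponent studies, yet it is multicomponent itself: the desk and the nudges always occur together.

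The nudges are not just operating instructions for the desk. {11a} describes tips on various ways to interrupt sitting, together with social support and social modelling. {18a} computes the activity variables over the whole waking day, not only over hours at the desk. The nudges could therefore change sitting time and transitions without any use of the desk.

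What is at stake is the conclusion. The Discussion addresses employers and policy makers deciding whether to invest in desks. If a positive result is reported as the effect of the desk, an employer who buys desks without the prompts has no evidence from this trial about what to expect.

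**Working it through.** The question is what each arm receives in months 1 to 6, and no stated figure needs to be reproduced. The components, from the abstract, {6b}, {11a} and {11c}:

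| Component | Intervention | Control | Differs? |
|---|---|---|---|
| Psychoeducational session | yes | yes | no |
| Sit-stand desk | yes | no | yes |
| Motivational nudges | yes | none | yes |
| Demonstration, ergonomic information, standing guidance, flyer | yes | no | yes |

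**Nudge count.** {11a} gives 4 in month 1, 2 in the second and third months, then one a month to the end of month 6.

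- If 2 applies to each of months 2 and 3: 4 + 2 + 2 + 1 + 1 + 1 = 11.
- If 2 is the total for the two months: 4 + 2 + 1 + 1 + 1 = 9.
- Control: 0 on either reading.

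**What the contrast identifies.** Write D for the effect of the desk with its set-up guidance, N for the effect of the nudges, and I for any interaction between them. The psychoeducational session is common to both arms and forms the background against which all three are defined. The expected difference between arms at 6 months is

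Δ = D + N + I.

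This is one equation in three unknowns. Separating D would need an arm with the desk and no nudges; separating N would need nudges and no desk. The trial has neither. Δ is estimable and D is not, whatever model is fitted.

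**Abstract against body.** The abstract lists the session as an intervention component and describes control as working as usual. The body gives the session to both arms. On the body's account, the comparator is psychoeducation alone.

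**Prompts after month 6.** {11a} schedules nudges to the end of the intervention, and the Discussion gives their duration as 6 months. {30}, under a heading on post-trial care, can be read in two ways: prompts delivered during the intervention with a long-term aim, or prompts delivered after it ends. On the first reading, the 9-month assessment in the intervention arm follows 3 months without desk or prompts. On the second, it follows 3 months without the desk but with prompts.

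**Feedback.** {11a} places feedback to all participants at the end of the intervention and of follow-up, and {18b} also says it comes at the end for everyone. {18b} then says that controls receive it only at the second assessment, because feedback at baseline could alter their behaviour. Singling out controls leaves open whether the intervention arm receives it earlier; no sentence says that it does.

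**The case against.** The strongest reply is that nothing is hidden. The abstract names the prompts as part of the intervention and states that controls get none, and the Discussion itself mentions the prompts shortly before the disputed sentence. Allocation, outcomes and analysis are unaffected, and the package effect is a legitimate target. All of this stands. It limits the point to what may be claimed, but it does not rescue the isolation claim.

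It can also be said that the demonstration, ergonomic advice, build-up guidance and flyer are largely part of supplying a desk. That is fair. The nudges are the decisive co-intervention, and the point holds on them alone.

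A reader might infer more than the documents support:

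- **Baseline feedback went to the intervention arm only.** The wording in {18b} permits this reading but does not establish it, and {11a} and {18b} both place feedback at the end for everyone.
- **Prompts definitely continue after month 6.** The parenthesis in {30} may describe the aim of the prompts and not their delivery date. The absent stimulus during follow-up is defined in {11a} as the desk, so that phrase does not settle the matter.
- **The maintenance conclusion is wrongly credited to the desk.** The protocol promises data on whether habits persist once the desk is gone, and {11a} openly uses the nudges to help internalise the routine. It nowhere credits persistence to the desk alone.
- **The documents put a size on the nudges' share.** To say that it could be anything from none to all of the difference only restates that the share is not identified.

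**Conclusion.** The isolation claim in the Discussion is wrong as written. The 6-month contrast is sit-stand desk plus motivational nudges and guidance versus psychoeducation alone. The intervention arm is scheduled to receive 11 nudges (or 9) and the control arm none. The package effect is estimable; the effect of the desk alone is not, and no later analysis can recover it.

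This rests on the nudges going only to intervention participants, as the abstract and {11a} both say, and on their being able to influence the outcome, which is the protocol's own reason for including them. It does not depend on how the prompt and feedback passages are resolved. Those two are requests for clarification and are not established faults.

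**What to change.** 1. Delete the claim in the Discussion that the trial isolates the impact of the desk.
2. State the contrast in the abstract, Objectives {7} and the conclusions as sit-stand desk plus motivational prompts and guidance versus psychoeducation alone.
3. Correct the abstract so that the psychoeducational session is shown as given to both arms, in line with {6b}, {11a}, {11c} and the Discussion.
4. Reconcile {30} with {11a} and the Discussion on whether prompts are delivered after month 6, and word the follow-up conclusion to match what was actually delivered.
5. Clarify in {18b} whether the intervention arm receives baseline feedback before controls do. Trial status says the intervention is already under way, so this may no longer be open to change; report any difference in feedback as a further part of the package.
6. State whether the two nudges for months 2 and 3 are per month or in total.

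The cost is wording and a check of what was delivered. No change to sample, allocation or analysis is needed. The price is a narrower conclusion: the trial can support the package but not the desk on its own.

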## Trial status

The current protocol version is dated 11/2/2023. The recruitment began on the 1st of January 2023 and ended by the end of February 2023. On the 1st of March, the intervention kicked off and is currently ongoing. Two more moments of assessment will still occur. Due to some delay in the revision of the final draft of the manuscript, we were not able to submit the manuscript prior to the last participant being recruited.

## Data Availability

Anonymized trial data will be available for non-commercial research purposes only upon request to the PI.

## Abbreviations

BDNF: Brain-derived neurotrophic factor
BMI: Body mass index
CONSORT: The Consolidation Standards of Reporting Trials
CVD: Cardiovascular diseases
DEBQ: Dutch Eating Behavior Questionnaire
LIPA: Light-intensity physical activity
PA: Physical activity
PhA: Phase angle
PI: Principle investigator
RCT: Randomized controlled trial
SB: Sedentary behavior
TFEQ-R21: Three-Factor Eating Questionnaire
UK: United Kingdom
USA: United States of America
VL: Vector length
WHO: World Health Organization
WHOQOL-BREF: World Health Organization Quality of Life Instrument-Abbreviated Version
